
### Interventions

Metronidazole/placebo: Treatment regimens were developed on their own according to each centre’s metronidazole specifications, which required maintenance of metronidazole plasma concentrations for subjects in the experimental group to be > 0.01 μG/ml, and the duration of administration was tentatively set at 5 years (i.e., the time of the outcome of this experiment).

The chemotherapy regimen is eFOLFOX_6_:

Oxaliplatin 85 mg/m^2^ IV infusion for 2 h, D1; leucovorin 400 mg/m^2^ IV for 2 h, D1; fluorouracil 400 mg/m^2^ IV bolus on D1 followed by 1200 mg/m^2^/DX2 continuous IV infusion (total 2400 mg/m^2^ over 46–48 h infusion). This process was repeated every 2 weeks for a total of 24 weeks (Table 1).

**Table 1 Tab1:** Chemotherapy regimen

Drug name	Dose	Timing of the drugs (a total of 28 days/cycle)							
		Pre-operation	Post-operation						
		D3–D1	D1	D2	D3–D14	D15	D16	D17–D21	D22–D28
Metronidazole/placebo	1 g	√	√	√	√	√	√	√	-
Oxaliplatin	85 mg/m^2^		√	-	-	√	-	-	-
Leucovorin	400 mg/m^2^		√	-	-	√	-	-	-
Fluorouracil	400 mg/m^2^		√	-	-	√	-	-	-
Fluorouracil	2400 mg/m^2^(total)		√		-	√		-	-

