#### Secondary outcomes

Postoperative complication rates: Postoperative complications will be classified according to their impact and the required management (e.g., medical treatment, reoperation, drainage), as proposed by Clavien–Dindo. Complications will be assessed at the 30-day follow-up; ancillary studies will assess complications at the 60-day and 5-year follow-ups. The Cumulative Complication Index will also be computed to assess the global burden of complications on each patient.Complete postoperative recovery: number of days between admission and when the patient is suitable for discharge.Unplanned secondary surgeryReadmission: need for any unplanned readmission after discharge for any reason.1-year, 3-year and 5-year survival ratesRelapse-free survival (RFS)Overall survival (OS)

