### Data collection, management, and analysis

#### Clinical data

Clinical data from patients will be obtained by medical staff and recorded on an online electronic platform (Http://www.medresman.org.cn) and in the CRF table. The sample will be coded, and the patient's identity will be known only by the attending physician. The clinical data will include the following: general patient information, past medical history, past surgical history, laboratory examination results, imaging results, surgery details, postoperative infection rate, incidence of postoperative complications, incidence of anastomotic leakage, and 30-day readmission rate after surgery. The timing and processing of the above-recorded contents will all be reflected in the CRF table, and the laboratory examinations will mainly assess preoperative and postoperative routine blood and inflammatory indicators (Table 2).

**Table 2 Tab2:** CRF table

Stage	Pre-operation		Intra-operation	Post-operation						
Follow-up period	14–3 days	3–1 days		1–14 days	30 days	1–12 months	12–24 months	24–36 months	36–48 months	48–60 months
Baseline data collected	√	-	-	-	-	-	-	-	-	-
Inclusion and exclusion	√	-	-	-	-	-	-	-	-	-
Sign informed consent	√	-	-	-	-	-	-	-	-	-
Group determination	√	-	-	-	-	-	-	-	-	-
Physical examination	√	-	-	-	√	√	√	√	√	√
Imaging examination	√	-	-	-	-	√	√	√	√	√
laboratory examination	√	-	-	-	√	√	√	√	√	√
First administration	-	√	-	-	-	-	-	-	-	-
Administration	-	-	-	√	√	√	√	√	√	√
Postoperation pathology	-	-	-	√	-	-	-	-	-	-
Safety observation	-	-	√	√	√	√	√	√	√	√
Record adverse events	-	-	√	√	√	√	√	√	√	√
Other works	√	√	√	√	√	√	√	√	√	√

A detailed description of the above data is shown in the CRF table.

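### Table 1 counts study drug and chemotherapy on one surgery-anchored day axis, so the first cycle as printed puts FOLFOX on postoperative days 1 and 15

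*Protocol article*

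**What the plan says.** In the protocol article, Interventions, Table 1 has one set of eight day columns, headed "Timing of the drugs (a total of 28 days/cycle". One column (D3–D1) stands under pre-operation. The other seven (D1, D2, D3–D14, D15, D16, D17–D21, D22–D28) stand under post-operation.

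- Metronidazole/placebo is ticked in the pre-operation column and at post-operation D1 to D21, with a dash at D22–D28.
- Oxaliplatin, leucovorin, bolus fluorouracil and infusional fluorouracil are each ticked at post-operation D1 and D15.

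The text above the table assigns the chemotherapy drugs to D1 without tying D1 to surgery, then adds: "This process was repeated every 2 weeks for a total of 24 weeks".

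Table 2 (Clinical data) ticks "First administration" at 3–1 days before operation, ticks further administration from 1–14 days after it, and ticks "Postoperation pathology" only at 1–14 days after operation.

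**The concern.** The two kinds of treatment need different clocks. Study drug begins before the operation and carries on straight after it. Adjuvant chemotherapy begins at a separate date, once the patient has recovered and the stage is known. Table 1 gives both the same clock and labels it by the operation.

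A site that follows the grid literally would give oxaliplatin and start a 46–48 h fluorouracil infusion on the day after bowel resection, possibly before pathology has been reported. The article's monitoring section says that investigators' compliance with the study plan and the drug dosage will be checked, so the printed table is the standard against which sites are held. What is at stake is patient safety, not the estimate of the treatment effect.

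**Working it through.** No figure in the plan has to be reproduced. The check is a reading of two tables and a count of days.

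**Alignment.** Table 1 has 1 + 7 = 8 day columns. The study-drug, oxaliplatin and leucovorin rows each have 8 cells, so the ticks line up with their headers and a broken table does not explain the result.

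**Cycle arithmetic.** 24 weeks / 2 weeks = 12 infusions. 24 weeks × 7 = 168 days, and 168 / 28 = 6 cycles, each with infusions on D1 and D15 (6 × 2 = 12). As a cycle description the chemotherapy rows are consistent. The trouble is only where D1 is anchored.

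**Possible meanings of D1.**

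| Meaning of D1 | Study-drug row | Chemotherapy rows |
|---|---|---|
| First day after surgery | Agrees with Table 2 (start 3–1 days before, administration at 1–14 days after) | Infusions on postoperative days 1 and 15 |
| First day of a repeating 28-day cycle that begins after surgery | Agrees with Table 2, and explains the D22–D28 pause in a 5-year drug | First cycle unchanged: infusions on postoperative days 1 and 15 |
| First day of chemotherapy, at some later date | Table 1 then shows no dosing between surgery and that date, although Table 2 ticks administration at 1–14 days | Sensible |

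The first two meanings suit the study drug and give the early infusions. The third suits chemotherapy and removes the study drug's postoperative anchor. None suits both.

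**Pathology.** Table 2 allows pathology on days 1–14. An infusion on day 1 falls on the first day of that window, up to 14 − 1 = 13 days before pathology need be recorded. The day-15 infusion falls 15 − 14 = 1 day after the window closes, so only the first infusion is affected.

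**Share of the schedule.** Two of the 12 infusions, both in the first cycle, are ticked in Table 1 at these days. These are counts of days and say nothing about the size of any clinical effect.

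**The case against.** The strongest reply is that cycle days were meant. The header speaks of a 28-day cycle. The text uses D1 as a regimen day and does not mention surgery. The study-drug row pauses at D22–D28 although the drug is given for 5 years, so that row must repeat and cannot be only a count of days since surgery. On this view, post-operation simply names the treatment phase.

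Most of this stands as an account of intent, and cycle days are the likelier meaning. It does not repair the table. The first cycle still has to begin somewhere, and Table 2 has study drug being given within 14 days after the operation. If the cycle is shared, chemotherapy starts on the first day of that same post-operation sequence.

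A second reply is that the interval from surgery to chemotherapy is a detail that a condensed article leaves to the full protocol. Figure 1 and the full protocol are not shown and may give a start day. That would excuse silence. Here the article prints a specific grid that ties the infusions to the operation, and the point is confined to that grid.

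Three stronger readings are tempting, and the documents do not support them.

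- A reader might infer that chemotherapy is intended on the day after surgery. The header and the study-drug pause suggest otherwise.
- A reader might infer that patients would be infused without any postoperative check. In Table 2 the row "Physical examination" and the laboratory row are dashed at 1–14 days and next ticked at 30 days, and the 2-week repeat would put a third infusion on day 29, also before that visit. But Table 2 is a recording grid for the CRF. It ticks safety observation and adverse-event recording at 1–14 days, and concomitant care is unrestricted, so routine pre-dose checks are not excluded.
- A reader might infer that complication results are compromised, since "Complications will be assessed at the 30-day follow-up". Complications are graded by Clavien–Dindo, the Safety section gives five causality criteria, and both arms share the schedule. Nothing shown supports a failure of grading or attribution, or a bias between arms.

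**Conclusion.** The point holds as a defect in a printed dosing table, and it should be fixed. In the first cycle, Table 1 as printed places all four chemotherapy rows on postoperative days 1 and 15, and the day-1 infusion may come before the pathology result.

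This rests on two assumptions. One is that Table 1 and Table 2 are meant to describe the same study-drug dosing around surgery. The other is a clinical judgement, not a figure from the documents: that cytotoxic infusion on the day after bowel resection is not wanted. The article gives no risk figure for early infusion, so no size of harm can be stated. An experienced oncologist would probably override the grid, but a cytotoxic schedule should be safe to follow as written. Confidence is medium, because the intended start day may be stated in material not shown.

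**What to change.** - Keep the metronidazole/placebo row counted in days from surgery.
- Relabel the oxaliplatin, leucovorin and two fluorouracil rows as days of a 28-day chemotherapy cycle counted from a separate C1D1.
- Add one sentence: C1D1 follows surgical recovery, availability of the pathology result and routine pre-chemotherapy checks, within a window that the clinical team sets. No day is proposed here, because the documents give no basis for one.

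The cost is new row labels and one sentence. It needs no extra patients and no change to the analysis. A new CRF field for the chemotherapy start date is not needed to make this correction.

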### Relevant concomitant care and interventions

There are no restrictions regarding concomitant care during the trial.

### Outcomes

#### Primary outcome

Efficacy will be measured in terms of the incidence of postoperative liver metastasis within 5 years after surgery.

Assessment will be conducted by in-person visits; should the status of the pandemic impact the study with no possibility of performing in-person 5-year follow-up appointments, telemonitoring might be considered using validated tools.

Considering that the dose of metronidazole is predicted in the form of a hypothesis, the incidence of drug-related adverse events will be regarded as one of the main indicators of this study.

#### Secondary outcomes

Postoperative complication rates: Postoperative complications will be classified according to their impact and the required management (e.g., medical treatment, reoperation, drainage), as proposed by Clavien–Dindo. Complications will be assessed at the 30-day follow-up; ancillary studies will assess complications at the 60-day and 5-year follow-ups. The Cumulative Complication Index will also be computed to assess the global burden of complications on each patient.Complete postoperative recovery: number of days between admission and when the patient is suitable for discharge.Unplanned secondary surgeryReadmission: need for any unplanned readmission after discharge for any reason.1-year, 3-year and 5-year survival ratesRelapse-free survival (RFS)Overall survival (OS)

### Randomization/assignment of interventions

Randomization was stratified by centre. Once informed consent is obtained, randomization will be performed via a centrally managed database. After receiving the patient grouping information, designated researchers will prepare trial drugs or placebo for patients according to the assigned group. In this process, only the researchers are informed about the grouping of patients. They will sign a confidentiality agreement and will not participate in any other links of the trial to ensure that they will not have any impact on the study. After collecting all the data, the designated researcher named the two groups A and B. The analyst will analyse the primary and secondary results without knowing the group name. Only after the analysis of the primary and secondary results can complete blindness be eliminated and ineffective blinding events recorded (for example, the study nurse discloses the patient's specific medication to the doctor).

The nurses provided the patients with oral antibiotics for the experimental group and placebo for the control group in the ward.

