The long-term effects of metronidazole use cause serious side effects and have been reported as individual cases in recent years. The probability of developing peripheral neuropathy in patients who continue to take metronidazole for > 4 weeks (taking a total dose of > 42 g) for a long period of time is approximately 17.9% [11, 12]. According to calculations, the blood concentration is approximately 34–45 μg/ml when patients develop peripheral neuropathy, and nearly all patients experience symptom resolution after discontinuing the medication. Therefore, for this study, we set the duration of metronidazole administration to 5 years in our patients, and because anaerobes are extremely sensitive to metronidazole, the dosage was extremely low, and in addition to long-term regulatory follow-up, patients in this protocol only needed to maintain daily blood concentrations greater than 0.01 μG/ml, which can maximize patient safety. At the same time, all the studies with patients who showed drug-related adverse reactions were discontinued, which was included in the ITT set and not included in the PP set.

The aim of this prospective, single-centre, large sample, randomized controlled trial is to demonstrate that long-term oral antibiotics can effectively reduce the incidence of post-operative liver metastasis in patients with colorectal cancer. Secondary objectives included safety and acceptability of the drugs used, treatment-related morbidity and mortality, and relevant follow-up.

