### Study setting

This study is a prospective, single-centre, randomized, double-blind controlled study in which 300 patients will be randomly assigned to the test group or the control group in a 1:1 allocation ratio. The study protocol can be accessed at the chictr.org.cn website (ChiCTR2100046201). Figure 1 shows the trial flow chart.

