### Eligibility criteria

Patients who meet any of the following conditions will be included:Patients of both sexes between 18 and 80 years old;Colon cancer (cT_3-4__a_T_0-3_M_0_ [UICC/AJCC-8th Colon Cancer TNM tumour stage]), rectal cancer (cT_3-4_N_0-3_M_0_ or any CT/N + [UICC/AJCC-8th Rectal Cancer TNM tumour stage]) and patients diagnosed and treated directly with surgery at each study centre;Patients who voluntarily agreed to join this study and signed the relevant informed consent form after verbal discussion about the clinical trial and discussion of the intention of obtaining informed consent.Patients who meet any of the following conditions will be excluded:Taking various classes of antibiotic medications on their own or with medical advice for various reasons within 2 weeks before surgery;Previous diagnosis or current diagnosis of inflammatory bowel disease;Diagnosed with acute intestinal perforation or acute small intestinal diverticulum;Those with ischaemic colitis or infectious colitis were included in the diagnosis;Diagnostic finding of other comorbid local or systemic disease that requires anti-infective treatment;Two and more simultaneous surgeries;Had been diagnosed due to acute and chronic peritonitis or other infectious diseases that require anti-infective treatment in the perioperative period;Any acute physiological disturbance that indicates that the subject requires emergency surgery without elective surgery [e.g., need for preoperative mechanical ventilation, preoperative acute renal failure, preoperative systemic inflammatory release syndrome, and sepsis or septic shock];ASA was rated on a 5-level scale;Immunodeficiency, immunosuppression or autoimmune diseases (e.g., allogeneic bone marrow transplant patients within the last 5 years, taking immunosuppressive drugs, and SLE);The subject refused to sign an informed consent form to participate in the trial;Other scenarios in which normal cooperation with a physician was not possible for personal reasons or the investigator considered it unsuitable to participate in the experiment; andAll single-port laparoscopic procedures, transhiatal procedures, and various new surgical modalities need to be used.The terminating study criteria are as follows:Subject's violation of treatment principles after enrolment (such as violation of entry criteria, noncompliance with study treatment medication or surgical arrangements);Subject was inoperable for various reasons after enrolment (reasons to be recorded);Subjects had nonstudy-related complications, such as drug hypersensitivity reactions, after enrolment;Because of the occurrence of adverse events, after the judgement of the investigator, the subject was not considered suitable to continue with the trial (the reason for withdrawal was recorded);Subjects or the subject's legally authorized representative required withdrawal from the study;Subjects developed serious complications or intolerable adverse reactions; andThe subject was not available for elective surgery after enrolment due to exacerbation of intercurrent illness or other reasons;

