#### Statistical analysis

The association with the variables of interest will be compared between groups by means of Pearson’s chi-squared test or Fisher’s exact test, as appropriate and in the case of categorical variables. For continuous variables, Student’s *t* test for independent samples and the Mann–Whitney *U* test will be used for normally and nonnormally distributed variables, respectively.

The analysis for the primary end-point variable (incidence of postoperative liver metastasis) will be performed with an intention-to-treat approach. The absolute difference in terms of incidence will be computed, along with 95% confidence intervals, and will be expressed as relative risk or odds ratio, as appropriate for each outcome.

An interim analysis is planned, once 50% of the patients have completed their treatment (half of the patients per arm). The study can be suspended if the treatment superiority is statistically significant, with a *P* value set at <0.0052. The interim analysis will be performed in agreement with previously reported epidemiological and statistical criteria.

For the secondary variables, a similar approach will be used, using the effect estimate with a 95% confidence interval and the relative risk and odds ratio for categorical variables.

Any potential effects related to centres or surgeons will be assessed by means of mixed models. For the primary end-point variable, a bivariate and multivariate analysis will be performed to identify the potential effects of other variables.

The value for statistical significance at the final analysis was set at *P* < 0.05. Statistical analysis will be performed with SPSS 20. All the deviations from the original statistical plan will be described and justified. All subjects included in the study will be included in the analysis.

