#### Auditing

The project management team will meet once a month to review the progress of the trial. As patients may experience some side effects during long-term administration of metronidazole, the trial steering team at each sub-centre, assigned by the team leader unit, will review the follow-up of subjects at each centre every 2 to 3 months to prevent irreparable harm to patients due to doctors’ or nurses’ errors. The hospital ethics review committees will work together to form an independent data monitoring committee that will review the data from each sub-centre every 3 months and at the time of interim analysis (performed once 50% of the planned sample of patients completed the primary endpoint follow-up )to verify the safety of treatment in both arms.

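### The protocol calls the trial single-centre but stratifies by centre, models centre effects and refers to several centres; the number of centres must be settled and the primary analysis matched to it

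*Protocol article*

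**What the plan says.** Four places define one centre: the title, the Methods/design part of the abstract, the aim at the end of the Introduction ("The aim of this prospective, single-centre, large sample, randomized controlled trial") and Study setting ("This study is a prospective, single-centre, randomized, double-blind controlled study").

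The operational sections read otherwise:
- **Randomization/assignment of interventions:** "Randomization was stratified by centre". No other stratification factor is named.
- **Eligibility criteria:** "patients diagnosed and treated directly with surgery at each study centre".
- **Interventions:** each centre draws up its own treatment regimen.
- **Statistical analysis:** "Any potential effects related to centres or surgeons will be assessed by means of mixed models".
- **Data monitoring:** the committee covers all centres.
- **Auditing:** the independent committee "will review the data from each sub-centre every 3 months".
- **Plans for communicating important protocol modifications:** changes are passed on to the centres.

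The consent section is printed twice under the same heading. One version has staff at each centre obtaining consent; the other has staff obtaining it, with no mention of centres.

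Statistical analysis compares categorical outcomes by Pearson's chi-squared or Fisher's exact test. The primary endpoint is analysed by intention to treat, with an absolute difference and a relative risk or odds ratio. Separately, for that endpoint, "a bivariate and multivariate analysis will be performed to identify the potential effects of other variables". The covariates are not listed.

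**The concern.** The number of centres determines what the randomisation scheme does and what the analysis model must contain. Here the two halves of the protocol give different answers.

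If there is one centre, a scheme stratified only by centre is unstratified. The trial admits both colon and rectal cancer over a range of clinical stages, so factors likely to predict liver metastasis would be balanced only by chance. A random effect for centre would have one level and could not be separated from the intercept.

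If there are several centres, readers of the title and abstract are told the wrong design. Centre would also be a plausible source of variation, because regimens are set locally. It would be the stratification factor, yet the main test leaves it out. Where centres differ in risk, ignoring a stratification factor gives standard errors that are somewhat too large. That costs power but does not inflate the type I error.

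**Working it through.** **1. The two readings side by side**

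| Element | If one centre | If several centres |
|---|---|---|
| Title, abstract, aim, setting | correct | wrong |
| Stratification by centre | one stratum, empty | works as intended |
| Mixed model, centre part | not estimable | estimable |
| Mixed model, surgeon part | keeps its meaning | keeps its meaning |
| Unstratified chi-squared or Fisher test | matches the randomisation | ignores the stratification factor |
| References to each centre, all centres, sub-centres | wrong | correct |

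Neither column is free of error. The duplicated consent section is consistent with an incomplete edit from one design to the other, but it does not show which came last.

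**2. Inputs for the size of the consequence**
- 150 patients per arm (Sample size calculation basis and formula; 300 / 2 = 150).
- Background liver metastasis after resection of 15% to 25% (Introduction). I use 20%, the midpoint.
- Node-positive share p of 30% to 50%: assumption, not in the document.
- Risk gap between node-positive and node-negative patients of 20 points, with 10 points as the alternative: assumption, not in the document.

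**3. Chance imbalance without effective stratification**

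Standard error of the between-arm difference in the node-positive share = sqrt(2p(1 − p)/150).
- p = 0.30: sqrt(2 × 0.30 × 0.70 / 150) = 0.053. The 95% range is ±10.4 points, and the probability of a difference of 10 points or more is 5.9%.
- p = 0.50: sqrt(2 × 0.50 × 0.50 / 150) = 0.058. The 95% range is ±11.3 points, and the probability is 8.3%.
- For 15 points or more the probabilities are 0.5% and 0.9%.

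**4. Effect of a 10-point imbalance on the risk difference**
- 20-point gap: 0.10 × 0.20 = 2.0 points.
- 10-point gap: 0.10 × 0.10 = 1.0 point.
- Comparison: the standard error of the risk difference at 20% incidence is sqrt(2 × 0.20 × 0.80 / 150) = 4.6 points. The 95% half-width is 1.96 × 4.62 = 9.1 points, so a 2-point shift is about a fifth of it.

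**5. Precision gained by adjustment**

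Share of outcome variance explained = p(1 − p) × 0.20² / (0.20 × 0.80).
- p = 0.30: 0.21 × 0.04 / 0.16 = 5.3%.
- p = 0.50: 0.25 × 0.04 / 0.16 = 6.3%.

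The half-width falls by a factor of about sqrt(1 − 0.05 to 0.06), that is by about 3%, from 9.1 to roughly 8.8 points.

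**6. Why model adjustment and not cross-stratified analysis**

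With five centres (assumption), crossing centre, site and nodal status gives 5 × 2 × 2 = 20 strata averaging 300 / 20 = 15 patients. At 15% to 25% incidence that is about 2 to 4 events per stratum. Across the whole trial the same incidence gives 45 to 75 events if treatment has no effect, which can carry a model with a few covariates.

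**The case against.** The strongest reply is that only the contradiction is an error, and that the statistical criticism asks for more than a sound trial needs. Much of this stands.

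- **Stratification does nothing.** A reader might infer this from the title. The documents do not support it as a fact: it follows only if the single-centre label is right, and many sections imply that it is not.
- **Prognostic factors are left unbalanced.** Randomisation balances them in expectation. Only chance imbalance remains; the test is not biased, and the confidence interval already allows for it.
- **The analysis is unadjusted.** The protocol does plan a multivariate analysis of the primary endpoint. The covariate list may properly sit in a statistical analysis plan that is not shown, so its absence is no fault. What can be said is narrower: the stated purpose of that analysis is to find effects of other variables, not to estimate an adjusted treatment effect, and the main comparison as described is unadjusted.
- **The mixed model is meaningless in one centre.** Only its centre part is; surgeons can still differ within one hospital.
- **Tumour site and nodal status should have been strata.** That is a recommendation. A centrally randomised trial of this size is valid without them.

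The reply does not remove the core. The number of centres and the stratification factor are both stated, they conflict, and no unseen document is needed to see it.

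**Conclusion.** The protocol contradicts itself on a basic design fact, and the sections must be reconciled. Either way something has to change: with one centre, an empty stratum and a centre effect that cannot be estimated; with several, a false label and a main test that omits the stratification factor.

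The textual conflict is certain. The numerical consequence is modest and conditional: a 6% to 8% chance of a 10-point imbalance in nodal status, a shift of 1 to 2 points in the risk difference if it occurs, and an interval about 3% narrower with adjustment. These figures rest on the assumed node-positive share and risk gaps and on 20% incidence. They justify a low-cost improvement to the analysis and do not suggest that the trial's result would be invalid.

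**What to change.** 1. **State the number of centres once and make every section agree**, including the duplicated consent section.
2. **If there is one centre:** delete the centre stratum and the centre term from the mixed model, keep the surgeon term, and remove the references to other centres and sub-centres.
3. **If there are several:** correct the title, abstract, aim and study setting, and account for centre in the primary treatment comparison, for example as a model term, in place of an unstratified chi-squared or Fisher test.
4. **In either case:** pre-specify tumour site (colon or rectum) and clinical nodal status as covariates in the primary treatment comparison, in the protocol or the analysis plan, before unblinding. Use model adjustment, not full cross-stratification.
5. **Optional:** stratify future randomisation by these two factors. For patients already randomised, covariate adjustment alone is available.

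The cost is an editorial pass and one or two sentences on the analysis. Table 2 does not list the two covariates by name, but eligibility depends on tumour site and clinical stage, so both should be known before allocation; confirm that the case report form records them. Only the optional step touches the randomisation database.

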### Allocation concealment mechanism

The randomization was performed on a centrally managed database once informed consent was obtained.

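### Randomisation may precede the first dose by up to 13 days, so avoidable pre-dose losses fall inside the intention-to-treat comparison; randomising next to the first dose is a cheap improvement

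*Protocol article*

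**What the plan says.** **Trigger.** The section Randomization/assignment of interventions states: "Once informed consent is obtained, randomization will be performed via a centrally managed database". Allocation concealment mechanism repeats it: "The randomization was performed on a centrally managed database once informed consent was obtained". No later checkpoint, such as a confirmed operation date, is named.

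**Timing.** In Table 2 (Clinical data), the rows for consent, inclusion and exclusion, and "Group determination" are all ticked 14 to 3 days before surgery. The row "First administration" is ticked 3 to 1 days before surgery. Table 1 also starts study drug on pre-operative days 3 to 1.

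**Foreseen losses.** The termination criteria under Eligibility criteria include "Subject was inoperable for various reasons after enrolment" and "Subjects or the subject's legally authorized representative required withdrawal from the study". They also list patients who can no longer have elective surgery because of intercurrent illness or other reasons.

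**Analysis.** Under Statistical analysis, the primary comparison "will be performed with an intention-to-treat approach", and every included subject is to be analysed. The primary outcome is liver metastasis over the five years counted from surgery.

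**The concern.** A patient who is randomised and then lost before the first dose has received neither metronidazole nor placebo, yet belongs to an arm. Such a patient carries no information on the treatment contrast. If kept, as intention to treat requires, the patient shrinks the observed difference. If the operation never happens, the five-year clock never starts, so it is unclear what outcome to record.

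Losses of this kind before randomisation would cost the comparison nothing. The timing in Table 2 lets them fall after it. Part of the eligibility window can also lie after allocation. The exclusion for antibiotic use covers the two weeks before surgery, so for a patient randomised on day −14 nearly all of that period is still to come.

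The trial has 150 patients per arm, and the article gives no effect size, power or dropout allowance for that number. There is no visible reserve to absorb avoidable dilution.

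**Working it through.** **1. The gap.** Allocation is at days −14 to −3 and the first dose at days −3 to −1 (Table 2).
- Longest gap: 14 − 1 = 13 days.
- Shortest gap: 3 − 3 = 0 days.

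**2. The plan's own figure.** The section Sample size calculation basis and formula sets 300 patients, 1:1, by reference to two other trials and feasibility. It states no event rate, effect or power, so 300 cannot be reproduced. The calculation below is for orientation only.

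**3. Inputs.**
- From the article: n = 150 per arm; final significance level 0.05 (taken as two-sided); control risk p_C of 15% to 25%, from the Introduction's background range, with 20% as the central case.
- Assumed: relative risk 0.50 in treated patients, so p_T = p_C/2; share d lost before the first dose in each arm of 2%, 5% or 10% (6, 15 or 30 of 300).

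**4. Two ways of counting lost patients.**
- A: they carry the control risk. p_T′ = (1 − d)p_T + d·p_C, and p_C is unchanged.
- B: they count as non-events. p_T′ = (1 − d)p_T and p_C′ = (1 − d)p_C.

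In both, the risk difference becomes (1 − d)(p_C − p_T). At 20% against 10%, 10.0 points become 9.8, 9.5 and 9.0. The relative risk differs: under A it moves to 0.51, 0.525 and 0.55; under B it stays at 0.50.

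**5. Power.** Power = Φ[(Δ − 1.96·SE0)/SE1], where Δ is the risk difference between the two risks compared (p_C or p_C′ against p_T′), SE0 = √(2p̄(1 − p̄)/n) with p̄ their mean, and SE1 = √{(p₁(1 − p₁) + p₂(1 − p₂))/n}.

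At 20% control risk:
- d = 0 (0.20 v 0.10): SE0 = 0.04123, SE1 = 0.04082; (0.10 − 0.08081)/0.04082 = 0.470; power 68.1%.
- d = 10%, A (0.20 v 0.11): SE0 = 0.04179, SE1 = 0.04147; (0.09 − 0.08191)/0.04147 = 0.195; power 57.7%.
- d = 10%, B (0.18 v 0.09): SE0 = 0.03946, SE1 = 0.03911; (0.09 − 0.07734)/0.03911 = 0.324; power 62.7%.

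| Control risk | d = 0 | d = 2% (A / B) | d = 5% (A / B) | d = 10% (A / B) |
|---|---|---|---|---|
| 15% | 53.8% | 52.0 / 52.9% | 49.1 / 51.5% | 44.6 / 49.1% |
| 20% | 68.1% | 66.1 / 67.0% | 63.0 / 65.4% | 57.7 / 62.7% |
| 25% | 79.5% | 77.7 / 78.5% | 74.7 / 76.9% | 69.5 / 74.2% |

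**6. Excluding the lost patients instead.** With n = 150(1 − d) and the full effect, power at 20% control risk is 67.2%, 65.8% and 63.5%. Even an analysis set limited to dosed patients would not return to 68.1%, because those places among the 300 are already used.

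**The case against.** Several objections have force.

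- **The wording need not mean immediate randomisation.** Consent may be read as a precondition, and the two windows meet at day −3. A site could randomise and dose on the same day without departing from the text. This stands: 13 days is a maximum, not the typical gap. But nothing in the text steers sites towards the short end.
- **The allocation is used before the first dose.** The randomisation section has designated researchers prepare drug or placebo once they receive the grouping. This stands, and it justifies some lead time. It does not explain a window that opens 11 days before the earliest dosing day (14 − 3).
- **The termination criteria do not locate losses in this gap.** They apply to any time after enrolment, so they also cover the pre-operative dosing days, the operation and, for withdrawal, later follow-up. This stands. They show that such losses are foreseen, not how many occur before dosing.
- **Handling of never-dosed patients may be in an analysis plan that is not shown.** This is fair, and its absence is not criticised here. But analysis rules cannot restore the places already used (step 6).

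A reader might infer that the result is biased in favour of one arm. The documents do not support that: allocation is central and the trial double-blind, so pre-dose loss should be similar in both arms. A reader might also infer that the relative risk must drift to 0.51–0.55. That holds only if lost patients carry the control risk. Never-operated patients have no start for the endpoint, and if they count as non-events the relative risk does not move.

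**Conclusion.** The point holds as a cheap design improvement. The timing allows 0 to 13 days between randomisation and first dose, and losses in that interval enter the intention-to-treat comparison unexposed, some without a definable start for the primary outcome. The consequence is non-differential dilution of the absolute difference and reduced power.

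The size is unknown. Across the assumed losses of 2% to 10%, with relative risk 0.50 and 20% control risk, the power cost runs from about 1 point (68.1 − 67.0, at 2% loss as non-events) to about 10 points (68.1 − 57.7, at 10% loss with control risk). Neither the loss rates nor the effect come from the article. If few patients are lost before dosing, the cost is small. It is also smaller than the power problem already present: with no pre-dose loss at all, power under these assumptions is only 54% to 80%.

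**What to change.** - Keep consent, baseline data and the eligibility check at days −14 to −3.
- In Table 2, move the group determination tick to the column for 3 to 1 days before surgery.
- Reword Randomization/assignment of interventions and Allocation concealment mechanism so that randomisation takes place as close as practicable before the first dose, after eligibility has been rechecked and the operation confirmed.
- Record patients lost earlier in the screening log already provided under Data ascertainment. They then do not count towards the 300.

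The change is one table cell and two sentences, and it can apply to every patient not yet randomised. It leaves the dosing schedule untouched. The main cost is shorter notice for the designated researchers who prepare blinded supplies. It does not remove inoperability found at or after the first dose, so never-operated patients will still need a stated outcome rule.
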